#### Economic Measures

##### Workplace productivity loss

Sickness absence data (absenteeism) will be collected from company records after the last follow-up measurement. Presenteeism (reduced productivity while at work) was measured using the WHO Work Performance Questionnaire (WHO-HPQ)[49,50] and the PROductivity and DISease Questionnaire (PRODISQ) [51,52]. Participants were asked to complete these questionnaires at 3, 6, 9, and will be asked again at 12 months.

##### Work-related outcome measures

In addition to specific cost-measures, some work-related outcome measures will be evaluated, such as work satisfaction and organisational commitment.

##### Cost measures

Intervention costs include the costs for group meetings (i.e. costs for the trainer, housing, and materials), e-mail contacts with trainers, website hosting and maintenance, offering fruit and snack vegetables, and printed materials. Frequency and duration of group meetings and e-mail contacts were recorded by the trainers. Trainer and coach costs will be valued based on their salary. Other costs will be valued using invoices of contractors.

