**Methods/Design:**

The study population consists of highly educated workers in two Dutch research institutes. The intervention was systematically developed, based on the Intervention Mapping (IM) protocol, involving workers and management in the process. The workers' needs were assessed by combining the results of interviews, focus group discussions and a questionnaire with available literature. Suitable methods and strategies were selected resulting in an intervention including: eight weeks of customized mindfulness training, followed by eight sessions of e-coaching and supporting elements, such as providing fruit and snack vegetables at the workplace, lunch walking routes, and a buddy system. The effects of the intervention will be evaluated in a RCT, with measurements at baseline, six months (T1) and 12 months (T2). In addition, cost-effectiveness and process of the intervention will also be evaluated.

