#### Step 4 Program Development

##### Mindfulness training

Participatory focus groups were held to develop the mindfulness training program. The groups discussed the duration of the proposed sessions and 90 minutes was considered feasible. The training will last eight weeks, as is usual for mindfulness training [36]. Each of the eight sessions will take 90 minutes, which is shorter than the usual duration (2.5 hours), but in-company (i.e., in the workplace) mindfulness training of shorter duration has also proven to be effective [37]. The mindfulness training will be given by certified trainers.

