##### Behavioural components

Mindful VIP training behavioural components will be treasuring social relations [38,34] by getting in contact with colleagues in the training, performing acts of kindness for oneself (since being in a mild and friendly state is the core of mindfulness) [31], and performing acts of kindness to others [40,34]. The program will include homework exercises, such as (sincerely) complimenting a colleague each day and noticing what this does for oneself and for others.

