##### Productivity-related costs

Workplace productivity losses (i.e. absenteeism and presenteeism) will be valued using salaries of the participants.

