#### Economic Evaluation

The economic evaluation aims to determine the cost-effectiveness of the intervention compared to the usual care from the societal and employer's perspective. Also, the cost-benefit analysis will be performed from the employer's perspective. The time horizon will be one year, similar to the trial. Analyses will be performed according to the intention-to-treat principle. In the main analysis, missing data will be imputed using fully conditional specification [55]. Sensitivity analyses will be done to assess the robustness of the results.

First, the total societal and employer's costs will be estimated, and compared between the intervention and control group. The 95% confidence intervals will be estimated using approximate bootstrap confidence intervals [56]. Societal costs include all cost measures described in the method section. From the employer's perspective, only costs relevant to the company are included (i.e. intervention, referral, and productivity-related costs). For the cost-effectiveness analysis (CEA), incremental cost-effectiveness ratios will be calculated by dividing the difference in costs between both groups by the difference in effects on the primary outcome measures (societal perspective) and work-related outcomes measures (employer's perspective). Bootstrapped cost-effect pairs will be graphically presented on cost-effectiveness planes [57]. Cost acceptability curves will be generated, showing the probability for cost-effectiveness of the intervention at various ceiling ratios. Also, a cost-benefit analysis (CBA) will be performed in which the incremental intervention and referral costs will be compared to the incremental productivity-related costs.

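### No cost category in the economic evaluation includes participants' time in the eight 90-minute sessions, so incremental cost is understated to the extent that sessions fell in paid working time

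*Protocol article*

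**What the plan says.** All references are to the protocol article.

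- **Intervention costs** (under Cost measures) are set out as follows: "Intervention costs include the costs for group meetings (i.e. costs for the trainer, housing, and materials), e-mail contacts with trainers, website hosting and maintenance", then fruit and snack vegetables and printed materials. Trainers and coaches are valued at their salaries and everything else from contractors' invoices. On time data: "Frequency and duration of group meetings and e-mail contacts were recorded by the trainers".
- **Productivity** (Productivity-related costs): "Workplace productivity losses (i.e. absenteeism and presenteeism) will be valued using salaries of the participants". Workplace productivity loss takes absenteeism from company sickness records and describes presenteeism as reduced productivity while at work.
- **Participant costs**: sports membership fees and sports equipment only.
- **Perspectives** (Economic Evaluation): the societal set is every cost measure described in the methods. For the employer, "only costs relevant to the company are included (i.e. intervention, referral, and productivity-related costs"). The cost-benefit analysis sets incremental intervention and referral costs against incremental productivity-related costs.
- **Training load** (Mindfulness training): "Each of the eight sessions will take 90 minutes". The abstract adds that training is "followed by eight sessions of e-coaching", and Behavioural components says: "The program will include homework exercises". No duration is given for e-coaching or homework.

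**The concern.** Attending the training takes workers' time. If that time is paid, the employer bears the cost and it is also a cost to society. The cost lists provide no place for it.

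The effect runs in one direction. Strengths and Limitations says that training and e-coaching are accessible only to the intervention group, so leaving out the time can only lower that arm's cost relative to control. The treatment of time is also uneven: a change in productive time after the training is priced at participants' salaries, whereas paid time spent in the training would be priced at zero.

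What is at stake is the economic evaluation, which is a declared aim: the employer's cost-benefit result and the incremental cost-effectiveness ratios from both perspectives. The analysis of work engagement, the primary endpoint, is not touched.

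**Working it through.** The article states no cost figure, so there is none to reproduce. The check has two parts.

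**1. Does any category pick up session time?**

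| Category | Content as stated | Session time included? |
|---|---|---|
| Intervention: group meetings | trainer, housing, materials (a closed bracket) | No |
| Intervention: other items | e-mail contacts, website, fruit and vegetables, print | No |
| Intervention: valuation rule | trainer and coach salary; otherwise contractors' invoices | No; employees' hours produce no contractor's invoice |
| Referral | occupational health services used after referral | No |
| Health care | care use and medication | No |
| Productivity | sickness absence; reduced productivity while at work | Not as defined; spill-over into presenteeism answers cannot be excluded |
| Participant | sports fees and equipment | No |

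Both perspectives are built from these categories, so session time enters neither.

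**2. How large could the omission be?**

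Inputs from the article: 8 sessions, 90 minutes each, 129 participants in the intervention arm.

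Assumptions, because the article gives no figure: hourly wage w = EUR 20-50, attendance a = 50-100%, share of session time that is paid s = 0-100%.

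- Hours per full attender: 8 x 1.5 = 12 h.
- Upper limit for the arm: 12 x 129 = 1,548 h.
- Omitted employer cost per participant: 12 x a x w x s.

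| Paid share s | Low end (a = 50%, w = 20) | High end (a = 100%, w = 50) |
|---|---|---|
| 100% | 12 x 0.5 x 20 = EUR 120; x 129 = EUR 15,480 | 12 x 1 x 50 = EUR 600; x 129 = EUR 77,400 |
| 50% | EUR 60; x 129 = EUR 7,740 | EUR 300; x 129 = EUR 38,700 |
| 0% | EUR 0 | EUR 0 |

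Homework and e-coaching time would come on top, but cannot be sized.

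**Scale against a counted item.** Trainer session cost per participant is 12 x trainer rate / group size. With an assumed EUR 50-150 per hour and groups of 8-20, it runs from 12 x 50 / 20 = EUR 30 to 12 x 150 / 8 = EUR 225. If sessions were paid time, the omitted item could therefore equal or exceed a main component that is counted.

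**The case against.** **Paid time is not established.** This is the strongest point, and it stands. A reader might infer from the in-company setting that sessions were in working hours and conclude that the employer's analyses are biased outright. The documents do not support that. The article glosses the term only as a location, in a remark about shorter courses: "in-company (i.e., in the workplace) mindfulness training of shorter duration has also proven to be effective". If all sessions were in own time, the employer omits nothing.

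**The article is a condensed account.** The cost list opens with a verb of inclusion, and unspecified sensitivity analyses are planned, so a fuller plan might cover this. That carries some weight but does not remove the point. The article does not merely stay silent: it closes the group-meeting bracket, gives a valuation rule for everything else, closes the productivity and employer lists, and builds both perspectives from them. An analyst who follows those rules will leave session time out.

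**A reversed result is not demonstrated.** A reader might also infer that the omission turns a net loss into an apparent gain. The documents give no intervention cost, productivity gain or expected return, so this cannot be shown.

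**The repair has practical limits.** These also stand. The trainers' records are described at the level of meetings; individual attendance records are not mentioned. Nothing says that the paid or unpaid status of sessions was recorded. If lost work time during training is reflected in the presenteeism answers, adding the hours would count them twice. Whether own time should be valued at all is a costing convention to which the plan has not committed.

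**Conclusion.** The point holds conditionally. As the cost categories are defined, participants' session time is costed nowhere: 12 h per full attender and at most 1,548 h for the arm.

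- To the extent that sessions fell in paid time, incremental cost is understated in the employer's cost-benefit and cost-effectiveness analyses and in the societal analysis.
- If all sessions were in own time, the employer's analyses are unaffected by session time. The societal analysis is affected only if own time is given a positive value.

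With every session in paid time, the omission is about EUR 120-600 per participant. That range rests on an assumed wage and attendance and excludes homework and e-coaching; it is illustrative, not an estimate. The direction of the understatement is clear, but its effect on the final economic conclusion is not known.

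**What to change.** 1. State whether sessions, e-coaching and homework took place in paid working time.
2. Add session hours spent in paid time to the intervention costs, valued at participants' salaries, in both the employer and the societal perspective. The plan already uses those salaries for productivity losses.
3. Use individual attendance records if they were kept. Otherwise use the recorded session durations with a stated range of attendance.
4. Check that these hours are not also counted as presenteeism loss.
5. If the paid share is unknown, show results at 0%, 50% and 100%.
6. Value own time only in a societal sensitivity analysis.

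The cost is a small extra calculation and a less favourable cost result. If the timing of sessions was not recorded, it must be recovered afterwards or handled through step 5. Nothing in the conduct of the trial or in the effect analysis changes.

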##### Referral costs

Trainers may refer participants to existing occupational health activities of the organisation, such as a consult with an occupational physician or with one of the in-company fitness professionals. The use of these options were reported by the participants at 6 and will be reported at 12 months, and will be valued using the contractors' invoices.

##### Health care costs

These include a general practitioner, allied health care, medical specialist, complementary medicine, hospitalisation, or medications. Data on resource use were and will be collected on a quarterly basis using retrospective questionnaires. Dutch standard costs [53] will be used to value health care utilization. If these are not available, prices according to each professional organization will be used. Medication use will be valued using unit prices provided by the Dutch Society of Pharmacy [54].

##### Productivity-related costs

Workplace productivity losses (i.e. absenteeism and presenteeism) will be valued using salaries of the participants.

##### Participant costs

Since the intervention stimulates participants to engage in regular physical activity, self-reported costs related to sports activities (membership fees and sports equipment costs) will be collected on a quarterly basis.

### Data Analysis

#### Baseline Characteristics

The baseline characteristics were analysed using descriptive statistics. All characteristics were tested for differences between the intervention and control group (with either independent sample t-test or chi-square test in case of normal distribution, and with the non-parametric alternatives in case of non-normal distribution), to determine randomization success.

#### Effect Evaluation

The effectiveness of the intervention will be analysed using a regression analysis (analysis of covariance) with the outcome measure at follow-up (T1: 6 months and T2: 12 months) as the dependent variable and adjusting for the baseline levels of the outcome measure. In addition, a Generalised Estimated Equations (GEE) analysis will be performed for the long-term effects (baseline to 12 months). All statistical analyses will be performed according to the intention-to-treat principle. For all analyses a two-tailed significance level of < 0.05 will be considered statistically significant. All analyses will be performed with SPSS 16.0 (SPSS Inc. Chicago, Illinois, USA).

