**Organisational based self-esteem**	Self regulation Goal setting Reinforcement	In-company mindfulness training Facilitate formulation of goals and reflection Providing positive feedback	Exercises aimed at self esteem at work. E-coaching: Employees formulate goals and reflect in logbook. Coach reads and stimulates reflection In-company mindfulness training: trainer provides positive feedback E-coaching: coach provides positive feedback
**Optimism**	Self regulation	In-company mindfulness training	Exercises aimed at optimism
**Social support**	Mobilising social support	Form groups or pairs	Group and duo discussions in in-company mindfulness sessions to discuss exercises. Finding a buddy is stimulated during the sessions.

**Table 2 T2:** Methods and strategies selected for increasing physical activity in leisure time of vigorous intensity

Key determinants	Theoretical method	Practical strategy	Tools and Materials
**Perceived behavioural control**	Self regulation Goal setting Reinforcement	In-company mindfulness training Facilitate formulation of goals and reflection Provide positive feedback	Exercises aimed at enlarging sense of control over behaviour and beliefs of efficacy. E-coaching: Employees formulate goals and reflect in logbook. Coach reads and stimulates reflection In-company mindfulness training: trainer provides positive feedback. E-coaching: coach provides positive feedback
**Perceived barriers**	Self regulation Goal setting	In-company mindfulness training Facilitate formulation of goals and reflection	Exercises aimed at reperceiving barriers and enacting on intentions. E-coaching: Employees formulate goals and reflect in logbook. Coach reads and stimulates reflection
**Social support**	Mobilising social support	Form pairs or groups	In-company mindfulness training in groups and oral instruction to form pairs to do discuss homework exercises
**Intention**	Self regulation	In-company mindfulness training	Exercises aimed at enacting on intentions

**Table 3 T3:** Methods and strategies selected for reducing sedentary behaviour at work

**Key determinants**	**Theoretical method**	**Practical strategy**	**Tools and Materials**
			

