### Sample Size Calculation

The sample size was based on finding an effect on work engagement, measured using the UWES [7]. The mean score for work engagement was 3.82 (sd = 1.1) on a scale from 0-6 [7]. An effect of a 10% increase in mean score was expected to be relevant and feasible. With a power of 90% and a two-sided alpha of 5%, both groups needed 175 workers. Accounting for a loss to follow-up of 25% over 12 months, each group needed 234 workers at baseline, thus an initial total of 468 workers for the two groups.

After recruiting 200 participants, the preliminary baseline characteristics were examined. It appeared that within our study population the standard deviation was smaller than the value reported in literature (0.83). With this knowledge, the power was recalculated, leading to a group size of 89 participants. When taking into account a 25% loss to follow-up, both groups needed 119 workers, thus a total of 238 workers to be included at baseline.

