Further, the intervention only aims at the individual worker. Ideally, a combination of individual and environmental changes was included. A meta-analysis of the effects of worksite physical activity and dietary interventions have namely shown greater effects on weight related outcomes for combined interventions compared to interventions based on one component (i.e. either individual or environmental changes) [59]. Nevertheless, because of the randomisation at individual level, possibilities to achieve and evaluate environmental changes within the Mindful VIP study were limited. Within these limitations, however, some environmental changes have been made on a social level, generating support in the group training, and in the physical environment by providing fruit. Concerning work engagement, on the other hand, it has been hypothesized that changes in environmental resources only yield short term effects because workers tend to quickly accommodate changes, which they have not initiated themselves based on their personal resources [34]. Therefore, it would be more beneficial to aim principally at the personal resources of work engagement and the individually based intervention targeting work engagement in the present study thus meets that hypothesis. However, this raises the question of whether the responsibility to be engaged or feel well at work can entirely be abdicated on the worker, especially since it is work-related--thus there is a need for further research.

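### The intervention arm is trained in groups, but the stated ANCOVA has no training-group or trainer term; if outcomes correlate within groups, the 5% level is exceeded.

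*Protocol article*

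**What the plan says.** Randomisation is at the level of the individual (Randomisation and Blinding). Only the intervention arm receives the eight weekly 90-minute sessions, which certified trainers give (Step 4, Mindfulness training). The same trainers carry out the e-coaching (E-coaching).

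Delivery in groups is deliberate. In Tables 2 and 3 social support is to be mobilised through "In-company mindfulness training in groups and oral instruction to form pairs to do discuss homework exercises". Table 1 uses group and paired discussion in the sessions as the route to social support, which is named as a key resource of work engagement, the primary outcome. Strengths and Limitations lists "generating support in the group training" among the environmental changes that were made. Controls have no matching structure.

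For the analysis, Effect Evaluation says: "The effectiveness of the intervention will be analysed using a regression analysis (analysis of covariance) with the outcome measure at follow-up" as dependent variable (6 and 12 months), adjusted for its baseline value. A GEE is added for long-term effects, and "For all analyses a two-tailed significance level of < 0.05 will be considered statistically significant". No training-group or trainer term is named.

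The Sample Size Calculation uses a mean, an SD, a 10% effect, alpha, power and 25% loss to follow-up: "With a power of 90% and a two-sided alpha of 5%, both groups needed 175 workers". This was later revised to 89 per group with an SD of 0.83.

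**The concern.** This is a partially nested design: independent individuals in one arm, individuals within training groups (and within trainers) in the other. If one group or trainer does better than another, members of a group share part of their outcome. The mean of the intervention arm is then less precise than its head count suggests. An ANCOVA that treats all participants as independent does not see this, so its standard error is too small.

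The confidence intervals and the 5% level of the primary comparison are at stake, and those of every secondary outcome analysed the same way. Too small a standard error makes a false claim of effect more likely. The protocol's own rationale, that support within the group helps to raise work engagement, makes some within-group correlation plausible.

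**Working it through.** **1. Do the plan's sample sizes contain a design effect?** The formula for independent participants is n per group = 2 × [SD × (1.960 + 1.282) / δ]².

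- Initial figure. "The mean score for work engagement was 3.82 (sd = 1.1) on a scale from 0-6" and "An effect of a 10% increase in mean score was expected to be relevant and feasible" give δ = 0.382. Then 2 × (1.1 × 3.2415 / 0.382)² = 174.3, so 175; 175 / 0.75 gives 234, or 468 in total. This matches exactly.
- Revised figure. With SD 0.83 and δ = 0.382 the result is 100, not 89. With δ = 0.405 it is 2 × (0.83 × 3.2415 / 0.405)² = 88.3, so 89; 89 / 0.75 gives 119, or 238 in total. A δ of about 0.405 is 10% of the pooled baseline mean in Table 5: (129 × 4.09 + 128 × 4.02) / 257 = 4.055. That δ is inferred; the section does not state it.

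Both figures follow from the independent-samples formula, with no room for a design effect.

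**2. Effect of grouping in one arm.** Let m be the group size and ICC the within-group correlation.

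- Design effect, intervention arm: DE = 1 + (m − 1) × ICC; control arm: 1.
- True SE / naive SE = √[(DE + 1) / 2].
- True two-sided alpha = 2 × [1 − Φ(1.96 / that ratio)].
- Power at n per group = Φ{δ / [SD × √((1 + DE) / n)] − 1.96}.

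For m = 12 and ICC = 0.05: DE = 1.55; ratio = √1.275 = 1.129; 1.96 / 1.129 = 1.736; alpha = 8.3%.

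Neither m nor ICC is documented, so the values below are assumptions. Power is for 89 per group, SD 0.83 and δ = 0.405; without grouping it is 90%.

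| m | ICC | DE | SE ratio | True alpha | Power |
|---|---|---|---|---|---|
| any | 0 | 1.00 | 1.000 | 5.0% | 90% |
| 8 | 0.01 | 1.07 | 1.017 | 5.4% | 89% |
| 8 | 0.05 | 1.35 | 1.084 | 7.1% | 85% |
| 12 | 0.05 | 1.55 | 1.129 | 8.3% | 82% |
| 15 | 0.05 | 1.70 | 1.162 | 9.2% | 80% |
| 15 | 0.10 | 2.40 | 1.304 | 13.3% | 70% |

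**3. Check by simulation.** The baseline-adjusted ANCOVA was simulated under no average effect, with 96 per arm, a baseline correlation of 0.6 and 20,000 runs per setting. It rejected in 4.8% to 5.1% of runs at ICC 0, in 7.2% at m = 8 and ICC 0.05, and in 8.2% at m = 12 and ICC 0.05. Adjusting for baseline does not remove the inflation.

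**4. Offsets to the power loss.**

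- 257 were randomised (129 and 128) against 238 planned. After 25% loss about 96 per arm remain (128 × 0.75 = 96).
- The sample size takes no credit for baseline adjustment. With an assumed baseline correlation of 0.5 the residual variance is 0.75 of the total, and 67 rather than 89 per group would suffice without grouping.
- Both together, at DE = 1.55: SE = 0.83 × √0.75 × √(2.55 / 96) = 0.117. Power is Φ(0.405 / 0.117 − 1.96), about 93%, or about 90% if δ = 0.382.

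**The case against.** The strongest reply is that the harm is conditional. The protocol gives no ICC, group size or number of groups. Because individuals are randomised, likeness among colleagues that predates the trial does not inflate alpha. If the programme changes nobody's outcome, the test stays valid. Inflation needs groups or trainers whose effects differ and average to zero. The sessions last eight weeks and outcomes are measured at 6 and 12 months, so whether a group effect persists is open. At ICC 0.01 with 8 per group the inflation is negligible. All of this stands, and it limits the size that can be claimed.

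A reader might also infer that the trial is underpowered. The documents do not support that: step 4 shows that plausible offsets can restore 90% power or more. Recruitment is also complete, so a restated sample size would change no decision.

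A reader might infer that the GEE certainly ignores the groups. Effect Evaluation does not state its clustering unit. As described, it neither answers the point nor proves it.

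Finally, an article is condensed and an analysis plan may exist. But the article does name its main model, and the arithmetic of the stated sample size shows that independence was assumed there.

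**Conclusion.** The point holds in conditional form. The main analysis as written keeps its two-sided 5% level only if training groups and trainers have no effect of their own. The protocol does not state that assumption, and it fits poorly with a programme that relies on group support. Under assumed group sizes of 8 to 15 and ICC 0.01 to 0.10, type I error runs from about 5.4% to 13.3%, with about 8.3% at 12 per group and ICC 0.05.

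It would go too far to say that the error rate is not held: with ICC = 0 it is, and the ICC is unknown. At 89 per group and the inferred δ of 0.405, power would fall from 90% to about 82% in the middle case, but a shortfall is not established once baseline adjustment and the 257 randomised are counted. Those offsets do nothing for the error rate, so the analysis should still be changed. Outcomes measured only in the accelerometer subsample of 100 have fewer people per group and so a smaller design effect.

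**What to change.** Before follow-up data are analysed, specify for the primary outcome, and for secondary outcomes analysed the same way:

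- a baseline-adjusted, partially nested mixed model with a random effect for training group in the intervention arm only (each control as a cluster of one) and small-sample degrees of freedom; or the regression with a cluster-robust variance by training group and a small-sample correction;
- whether trainer enters as a further level, since trainers also do the e-coaching;
- that intervention participants who did not attend are analysed in their assigned group, where one is recorded;
- the clustering unit of the GEE;
- that the ICC is reported with the results.

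Neither treatment nor recruitment changes. Confidence intervals become slightly wider if the ICC is positive, and little is lost if it is near zero. Group allocation must be retrievable. Cost measures says only that trainers recorded the frequency and duration of meetings and e-mail contacts, so it should be confirmed now that each participant's group and trainer are on file.
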